## Abstract

**Background:**

In the HPV FOCAL trial, we will establish the efficacy of hr-HPV DNA testing as a stand-alone screening test followed by liquid based cytology (LBC) triage of hr-HPV-positive women compared to LBC followed by hr-HPV triage with ≥ CIN3 as the outcome.

**Methods/Design:**

HPV-FOCAL is a randomized, controlled, three-armed study over a four year period conducted in British Columbia. It will recruit 33,000 women aged 25-65 through the province's population based cervical cancer screening program. *Control arm: *LBC at entry and two years, and combined LBC and hr-HPV at four years among those with initial negative results and hr-HPV triage of ASCUS cases; *Two Year Safety Check arm*: hr-HPV at entry and LBC at two years in those with initial negative results with LBC triage of hr-HPV positives; *Four Year Intervention Arm*: hr-HPV at entry and combined hr-HPV and LBC at four years among those with initial negative results with LBC triage of hr-HPV positive cases

**Discussion:**

To date, 6150 participants have a completed sample and epidemiologic questionnaire. Of the 2019 women enrolled in the control arm, 1908 (94.5%) were cytology negative. Women aged 25-29 had the highest rates of HSIL (1.4%). In the safety arm 92.2% of women were hr-HPV negative, with the highest rate of hr-HPV positivity found in 25-29 year old women (23.5%). Similar results were obtained in the intervention arm HPV FOCAL is the first randomized trial in North America to examine hr-HPV testing as the primary screen for cervical cancer within a population-based cervical cancer screening program.

**Trial Registration:**

International Standard Randomised Controlled Trial Number Register, ISRCTN79347302

## Background

Cervical cancer screening using cervical cytology (the Pap smear) has been an extremely successful public health intervention, achieving reductions in cervical cancer incidence of up to 80% where practiced effectively[1]. However, the Pap smear was introduced over 50 years ago and studies have now proven it has significant limitations. Data from some jurisdictions indicate that cervical cancer rates have reached a nadir, and meta-analyses indicate that the sensitivity of a single Pap test to detect cervical intraepithelial neoplasia (CIN) or invasive cervical cancer is less than 60%[2,3].

There is now ample evidence that infection with high-risk types of the Human Papillomavirus (hr-HPV) is a requisite intermediate step for the development of cervical cancer and its precursors[4,5]. On this basis, it has been proposed that testing for the presence of hr-HPV could improve cervical cancer screening. HPV testing is recommended for follow up of abnormal cytology in women over the age of 30 and for the surveillance of patients after colposcopic treatment for CIN[6]. When used as a primary screening tool in cross sectional studies, it has been demonstrated that hr-HPV testing has a higher sensitivity and negative predictive value (NPV) for CIN2 or worse (≥ CIN2) detection than either the conventional Pap smear or liquid based cytology (LBC), albeit with a lower specificity and positive predictive value (PPV)[7-12]. In recognition of this, one approach for screening would be to use hr-HPV testing as a **single primary screening test **with cytology reserved only for the triage of women having a positive test, especially following the advent of HPV vaccination[12,13]. This would offer several advantages over combined testing:

• Screening would be undertaken with the test having higher *sensitivity *(hr-HPV testing);

• 85-90% of women would be returned immediately to routine screening with a negative hr-HPV test without incurring the cost of cytology, which would be reserved only for those with a positive hr-HPV;

• The high-volume screening of samples would be undertaken with a non-subjective test that can be automated, while the subjective, labour-intensive test would be restricted to high-risk samples that could be examined with greater vigilance because of the reduced number to be interpreted;

• It represents a more robust screening approach that could serve the additional purpose of post-vaccination surveillance in the population[13];

• The recommended cervical cancer screening interval can be extended, as the long term risk of CIN3 or worse in women with a negative hr-HPV test is much lower than those who have a negative cytology, thus providing greater reassurance to women and also resulting in potential cost savings[10].

To examine these concepts, several international large randomized controlled trials (RCT) are being conducted in Europe and in Canada to evaluate HPV testing as part of primary cervical cancer screening[9,14-21]. With the exception of the Finnish Randomized Public Health Trial and phase 2 of the New Technologies for Cervical Cancer Screening (NTCC) trial in Italy, these trials have compared combined HPV and cytology testing vs. cytology alone as the primary screening intervention. The Phase 2 of NTCC and the Finnish trials are comparing HPV versus cytology as the primary screen, and both of these employ conventional cytology as opposed to liquid based cytology (LBC) which is replacing conventional cytology in several jurisdictions[14,20]. To date, there has not been a RCT of hr-HPV detection followed by cytology triage of hr-HPV positive women, compared to cytology alone in a population based screening program in North America, and no trials have utilized LBC. It is essential to properly evaluate this approach within the context of a population based cervical cancer screening program which would provide generalizable evidence to inform policy decisions concerning cervical cancer screening internationally.

This paper describes the design and preliminary screening results of the HPV FOCAL Trial. The primary objective of the HPV FOCAL trial is to establish the efficacy of hr-HPV testing followed by liquid based cytology (LBC) triage of hr-HPV-positive women compared to LBC followed by hr-HPV triage for cervical cancer screening with ≥ CIN3 as the outcome, through a comparison of the estimated decreases in cervical intraepithelial neoplasia (CIN 2/3) that can be achieved by each screening modality in successive screening rounds. The secondary objectives of this trial are to establish the appropriate screening interval for hr-HPV negative women, using the current standard of a 2-year recall interval for cytology negative women as the benchmark of acceptable risk in British Columbia; to establish the appropriate clinical follow-up for hr-HPV positive women; and to establish the cost-effectiveness of hr-HPV testing for primary screening, all within the context of a population based Canadian cervical cancer screening program. The results of this trial will demonstrate whether or not the use of hr-HPV testing as a single primary screening test within a population based cervical cancer screening program will be able to provide further reductions in the incidence of cervical cancer and its precursor lesions, allow the screening interval to be extended, and improve the cost-effectiveness of cervical cancer screening.

## Methods/Design

### Trial Design

HPV FOCAL is a three-armed, RCT over a four year period (Figure 1).

**Figure 1 F1:**
[figure not shown]
**HPV FOCAL: a three-armed, RCT over a four year period**.

**Control arm**: LBC at entry and again at two years; ASCUS cases are triaged with hr-HPV testing; combined LBC and hr-HPV at four years (exit screen) among those with initial negative results.

**Two Year Safety Check arm**: hr-HPV at entry; LBC at two years (exit screen) in those with initial negative hr-HPV results with LBC triage of hr-HPV positives at either round.

**Four Year Intervention Arm**: hr-HPV at entry with LBC triage of hr-HPV positives; combined hr-HPV and LBC at four years (exit screen) among those with initial hr-HPV negative results.

### British Columbia Population Based Cervical Cancer Screening Program

Since the 1960s, cervical cancer screening in British Columbia has been organized as a centrally administered program[22]. A single provincial laboratory (Provincial Health Services Laboratories) processes and interprets Pap test samples from all clinicians in the province. A unified set of recommendations for the management of women with abnormal Pap tests is produced by the British Columbia Cancer Agency (BCCA), and is communicated to the healthcare providers with the Pap test results. BCCA also manages a coordinated follow-up system involving regional colposcopy clinics across the province for women with abnormal Pap tests. BCCA's Cervical Cancer Screening Program maintains a single data structure linking all Pap test results and disease outcomes, and provides overall program administration and coordination of promotion, recruitment, follow-up reminder system, follow-up tracking, quality management, program evaluation and research support.

### Study Population and Recruitment

Women aged 25 to 65, registered with Medical Services Plan in British Columbia, who receive care from a participating family physician (FP) for routine cervical screening are eligible. Exclusion criteria are: a history of histologically proven CIN2 or worse requiring treatment in the last five years; a history of histologically proven invasive cervical cancer; a Pap smear within the preceding twelve months; no cervix; pregnant at time of enrolment; HIV positive or on immunosuppressive treatments; or unwilling or unable to provide informed consent.

Women are invited to participate in the study when they present for cervical cancer screening and are deemed eligible to participate by their FP or when pre-identified as being due for screening from the BCCA centralized provincial cytology database. For the pre-identified, the FP office sends the woman a study package that includes an invitation letter, a study information pamphlet and the informed consent form. The invitation letter requests women to phone their FP to make an appointment for their cervical screening test and also provides them with the opportunity to contact, or be contacted by study staff to learn more about the trial and decide on participation. All participants are consented by their FP and are asked to complete an epidemiologic questionnaire. A financial implications questionnaire is also completed by a random sample of participants. Full cervical cancer screening history is available through data linkage to the cervical cancer screening program, and HPV vaccination status is self reported.

### Study Protocol (Figure 1)

In addition to the control arm and the intervention arm, a 'two year safety-check' arm is included in this trial. At the time of the trial design, there were ethical concerns identified in changing the screening interval at the same time as changing the primary screening tool in a clinical trial. To that end, we included a safety check arm, to examine the safety of hr-HPV testing within the usual screening interval. This information will be used by the data safety monitoring board to verify the safety of hr-HPV testing at the two year interval and infer the suitability of the intervention arm as the trial proceeds.

Two samples are collected during the initial screening appointment. Specimen1 (LBC) is collected first with the ThinPrep^® ^Broom-like collection device and is placed in a ThinPrep^® ^PreservCyt vial (Hologic Inc, Bedford MA) and is used for all the HPV FOCAL trial testing. Specimen 2 is collected in Digene STM^® ^(Qiagen, Mississauga ON) and is frozen for future use. Both specimens are sent to the central laboratory in Vancouver, for trial testing (specimen 1) and for storage (specimen 2). Upon sample receipt, the woman is randomized to one of the three study arms and specimen 1 is aliquoted (Figure 1). For those allocated to hr-HPV testing arms, an aliquot is removed and processed using the Qiagen sample conversion kit, and tested using the Digene Hybrid Capture 2 (HC2) assay (Qiagen, Mississauga ON), which tests simultaneously for the presence of DNA from 13 hr-HPV types. Results are classified as hr-HPV negative, hr-HPV positive or unsatisfactory. LBC testing is conducted on specimen 1 using the ThinPrep^® ^collected device, according to the manufacturer's recommendations. Cytological evaluation and reporting follow the Bethesda classification system [23].

#### Colposcopy

If the woman's test results indicate that a colposcopy referral is recommended (Figure 1), this will be conveyed to the FP with the study sample results. All colposcopy examinations are performed at study-designated colposcopy clinics in Vancouver and Victoria to ensure consistency in diagnostic performance. Colposcopic examinations performed in British Columbia are highly standardized, and clinicians providing colposcopy adhere to a study-agreed protocol.

Women referred for colposcopy fall into the following major groupings:

a) Cytology: AGC (hr-HPV positive or not done);

b) Cytology: ASC-H or ≥ LSIL (hr-HPV positive or not done);

c) Cytology: ASC-US; (hr-HPV positive or persistent ASC-US which was initially hr-HPV negative).

Women are managed according to the standard provincial guidelines in the province of British Columbia[24]. Colposcopy is used to assess the highest grade lesion seen on the cervix and directed biopsy(s) is performed as well as an endocervical curettage when appropriate. The standard treatment for CIN2+ in British Columbia is an excisional treatment, most commonly loop electrosurgical excision procedure (LEEP) and occasionally cone biopsy

#### Histology

Pathological interpretation of biopsies is conducted at two centres which provide services to the participating colposcopy clinics. Pathologists are blinded to cytology and hr-HPV result when interpreting the slides. Histology results are stored in the same Laboratory Information System (LIS) as the cytology results.

Following standard practice, if there is significant discordance between the cytologic and histologic evaluation which would potentially influence patient management, the colposcopist contacts the laboratory to request review and correlation of the histology and cytology in order to resolve the discrepancy (e.g. a case where HSIL cytology is noted, but negative histology,) and determine an appropriate disease management strategy.

A review of exit screen histology is an essential component of the trial. Approximately 50% of exit screen histology results will undergo second review by senior study pathologists. If the primary and review histology results agree, this will be the final study diagnosis, but in the case of disagreement between primary and review histology, the slide will be referred to another senior pathologist. If this result agrees with either the primary result or first review the agreed results will be the final study diagnosis. If all 3 results are different, the final study diagnosis will be established by consensus between all three pathologists.

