### Analysis

#### Primary Outcome Measures

• Control and intervention arms: Cumulative incident ≥ CIN3 detected up to and including four years in both the control arm and the intervention arm

• Control and safety check arms: Incident ≥ CIN2 detected at two years. If the number of ≥ CIN2 in the safety-check group exceeds 0.8 times that in the control arm at the 2 year screen, then the trial will conclude and women in the four year intervention arm will be recalled at two years for their exit screen.

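### Second histology review follows the exit screen, so the two-year ≥ CIN2 comparison may set partly reviewed safety-arm lesions against unreviewed control-arm lesions

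*Protocol article*

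**What the plan says.** The Histology section of the protocol article gives the second review a formal role: "A review of exit screen histology is an essential component of the trial". Its scope is then stated: "Approximately 50% of exit screen histology results will undergo second review by senior study pathologists". If primary and review reads agree, that is the final study diagnosis. If they differ, a third senior pathologist reads the slide, and three different results go to consensus. No other route to a final study diagnosis is described.

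The Figure 1 legend places the exit screen at different times:

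- Safety check arm: "hr-HPV at entry; LBC at two years (exit screen) in those with initial negative hr-HPV results".
- Control arm: "LBC at entry and again at two years; ASCUS cases are triaged with hr-HPV testing", followed by "combined LBC and hr-HPV at four years (exit screen) among those with initial negative results". The control arm's two-year round is not called an exit screen.

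Under Primary Outcome Measures one comparison is "Control and safety check arms: Incident ≥ CIN2 detected at two years". A trial-level rule is attached: if the safety-arm number is more than 0.8 times the control-arm number, the trial concludes and women in the four-year arm are recalled at two years.

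**The concern.** Review is allocated by exit status, and exit status coincides with arm at the two-year screen. About half of the safety arm's two-year histology is open to regrading by this review; on the text as written, none of the control arm's is.

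Pathologists are blinded to cytology and hr-HPV results, which protects each reading. It does not equalise the number of readings per lesion between the arms. If review lowers or raises the ≥ CIN2 count on balance, the change enters the numerator of the ratio and not the denominator, so it does not cancel. At stake are a primary outcome and a decision on whether the trial continues as designed.

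The cumulative ≥ CIN3 comparison between control and intervention arms is touched to a lesser extent, because control-arm lesions found at two years also fall outside the review.

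**Working it through.** **Which lesions the stated review reaches**

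| Round | Control | Safety check | Intervention |
|---|---|---|---|
| Entry | not reviewed | not reviewed | not reviewed |
| Two years | not reviewed | about 50% (exit) | no routine screen |
| Four years | about 50% (exit) | – | about 50% (exit) |

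In the two-year comparison the arms differ completely in coverage. In the four-year comparison entry and exit rounds match, and only the control arm's two-year lesions differ.

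**Size in the two-year comparison**

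The article gives no regrading rate and no two-year ≥ CIN2 rate, so there is no stated figure to reproduce. What follows is an illustration.

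Inputs from the article:

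- Review fraction 0.5 (Histology).
- Trigger 0.8, on numbers of cases (Primary Outcome Measures).
- Test-negative shares at entry of 92.2% in the safety arm and 94.5% in the control arm (Preliminary Findings), giving a denominator ratio of 92.2/94.5 = 0.976.

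Assumptions:

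- Control-arm expected count C = 104. This is about 1% of 11,000 × 0.945 = 10,395 women. C = 52 is shown as a lower case.
- True rate ratio R, safety to control. The value 0.8 matches the 20% relative difference used for planning under Sample Size.
- Net change n in the ≥ CIN2 count among reviewed slides, from -20% to +10%.
- Independent Poisson counts.

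Formulas:

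- Review factor on the safety arm: f = 1 + 0.5n, so f = 0.90 at n = -20% and 1.05 at n = +10%.
- Safety-arm mean: C × R × 0.976 × f. At C = 104 and R = 0.8 this is 81.2 with no net change, 73.1 at n = -20% and 85.3 at n = +10%.
- Chance of crossing: P(S > 0.8K), where S is the safety-arm count and K the control-arm count, with mean C.

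| C | R | n = 0 | n = -20% | n = +10% |
|---|---|---|---|---|
| 104 | 0.9 | 74% | 46% | 84% |
| 104 | 0.8 | 43% | 19% | 56% |
| 104 | 0.6 | 2.4% | 0.5% | 4.5% |
| 104 | 0.5 | 0.1% | 0.0% | 0.3% |
| 52 | 0.8 | 45% | 27% | 54% |
| 52 | 0.6 | 8.0% | 3.3% | 11.4% |

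A milder n = -10% at C = 104 and R = 0.8 gives 30% instead of 43%.

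In terms of the threshold, a true ratio of case counts of 0.8/0.90 = 0.889 would on average be read as 0.80 at n = -20%, and 0.8/1.05 = 0.762 would be read as 0.80 at n = +10%. With the same review in both arms f appears above and below the line and cancels.

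**The case against.** The strongest reply is that the article never says which diagnosis feeds the trigger or the two-year outcome. It counts ≥ CIN2 cases and elsewhere requires histological confirmation. If primary reads are used in both arms, the trigger escapes the problem. The article is also condensed, and it does not expressly exclude control-arm two-year histology from review. This stands, and it makes the point conditional. It does not remove it: the article states the scope of review affirmatively, ties it to exit status, and defines no endpoint diagnosis other than the one that review can change.

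A second reply is that the effect is shown where it is largest, and that the third-reader rule dampens regrading. This also stands in part. At 104 control cases and true ratios of 0.6 or 0.5 the change is about 2 percentage points or less. The assumed n is the net change after all adjudication, and its true value is unknown.

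Two stronger readings may tempt a reader:

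- That the discordance procedure, in which a colposcopist can "request review and correlation of the histology and cytology in order to resolve the discrepancy", contradicts the blinding of pathologists. It does not. Blinding applies to reading the slides; the discordance check is a separate patient-management step, restricted to no arm, and nothing says it replaces the study diagnosis.
- That the cumulative ≥ CIN3 result is shown to be biased. Only control-arm lesions found at two years differ in review coverage, and the article gives nothing from which to derive a direction or size.

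**Conclusion.** The point holds conditionally. As written, the review follows the exit screen and so reaches about half of the safety arm's two-year histology and none of the control arm's. If final study diagnoses are used, the two-year ≥ CIN2 outcome and the 0.8 ratio rest on different ascertainment in the two arms.

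Near the threshold the consequence could be material: 43% becomes 19% or 56% at a true ratio of 0.8 with 104 control cases. These figures depend on assumed case counts and regrading rates and show sensitivity, not an estimate of actual bias. The direction is unknown: net downgrading makes the trigger harder to cross, net upgrading easier. The effect on the cumulative ≥ CIN3 comparison is smaller in scope and unquantified. A reader should not conclude that the stopping decision is certainly biased, since the article leaves open which diagnosis it uses.

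**What to change.** State one diagnosis basis for the arms compared, before two-year cases are counted. Either option works for the two-year comparison and the trigger:

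1. Use the primary blinded read in both arms, and report reviewed diagnoses as a sensitivity analysis. This needs wording only. The downside is that the two-year comparison then rests on single reads, although the trial regards review as essential.
2. Draw the same review fraction from control-arm two-year histology, with the same adjudication steps and reviewers blind to arm and round. This keeps the reviewed diagnosis, at the cost of adding some reads or reallocating them among the existing reviewers.

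Option 2 also closes the gap in the cumulative ≥ CIN3 comparison, since control-arm two-year lesions would then be reviewed at the same rate as exit lesions. Under option 1, the plan should say separately which diagnosis the four-year comparison uses for those lesions.

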### Randomization and Blinding

A database has been developed specifically for the HPV FOCAL trial. Randomization occurs through this database when samples are received at the laboratory. At the time of randomization a Study Identification Number (SIN) is allocated to the participant. Samples are stratified by age and simple equal (1/3 probability) random allocation occurs at the laboratory. Upon randomization, study staff label and batch the specimens for initial processing (hr-HPV or LBC).

FPs and participants are blinded to study arm allocation. Participant results are communicated from the BCCA to the FP office as soon as they are known. If the participant's initial screening results (hr-HPV or cytology) are "negative" the report states "within normal limits". The report also states that the recommended follow-up for that participant will be communicated to the FP in two years' time. This ensures blinding is maintained for as long as possible and prevents any bias that may potentially occur from knowledge of negative results. If the screening results are hr-HPV and/or cytology positive, the results are communicated from the BCCA to the FP along with the recommended follow-up.

